### Data management and statistical analysis plan

The principal investigator and co-investigators will monitor data as it is acquired to ensure the quality of the data. Data monitoring and auditing will be performed on a monthly basis on RedCap. All information regarding experimental patients will be kept in a file cabinet in the office of the principal investigator. All data for presentation will be identified by a code number only. All data spreadsheets will be housed on the password-protected server at the lab and de-identified as described above. All MGH collaborators will have access to the de-identified data as needed for analysis and manuscript preparation.

For statistical analysis, we will assess intervention credibility and acceptability and track the number of patients who meet the study criteria, the number approached for enrollment, the number enrolled, reasons why patients chose not to participate, dropout rate, and reasons for dropout. These data will be summarized by standard descriptive statistics. For all participants in the trial, descriptive statistics will be provided to characterize recruited patients at baseline for treatment and control groups and ensure that balance is achieved by randomization. The presentation of the data will follow the CONSORT recommendations for reporting results of RCTs. Statistical procedures carried out use *α* = 0.10 as the significance level. All analyses will be performed using SAS, version 9.4 (SAS Institute, Inc.).

Although this is a pilot study, we do want to explore whether or not there is a difference between groups. Analyses based on the intent-to-treat principle are designed to examine the treatment effect of *L. reuteri* probiotics vs placebo at the end of the first stage of trial on primary outcomes, which are behavioral scores (i.e., ABC and SRS-2), behavioral testing results (i.e., eye-tracking and emotional face matching tests), and serum OXT changes. Since there are multiple primary outcomes, false discovery rate due to multiple comparisons will be taken into account. Per-protocol analyses for secondary outcomes will be performed based on available data due to relatively small sample size. Methods for secondary analyses conducted will be similar to primary analyses. Two-sample *t* tests will be performed on secondary outcomes as appropriate.

Gut microbiome data will be analyzed with the QIIME software package v. 2018.2.0 [30]. For short-chain fatty acid profiling, volcano plots will be generated displaying fold differences vs. significance adjusted for multiple testing. Two-sample *t* tests will be performed on outcomes, such as microbial relative abundances, alpha-diversity, and leading short-chain fatty acid metabolites as appropriate.

### Follow-up and compliance assessment

Follow-up evaluations will include compliance evaluation and safety assessments of potential adverse effects. Compliance will be assessed on a monthly basis via telephone check-in. Compliance to intervention will be also assessed by determining the number of capsules and sprays returned at each follow-up visit at week 12 and week 24 from the treatment packs dispensed. The adherence of this trial will be also assessed by (1) changes of serum OXT levels, (2) changes in microbial relative abundances and diversity, and (3) changes in fecal short-chain fatty acid metabolites.

### Safety and adverse effect reporting

Adverse reactions will be monitored on a monthly basis via self-report and telephone check-in, if guardians fail to complete online surveys. All adverse events will be reported to the Human Research Committee promptly in accordance with guidelines. Randomized patients will have to be immediately withdrawn from the trial if they complain about serious adverse events.

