**Fig. 1 Fig1:**
[figure not shown]
Study design. OXT oxytocin, ABC Aberrant Behavior Checklist, SRS social responsiveness scale, GSI gastrointestinal severity index, Gaba gamma-aminobutyric acid, IL interleukin, TGF tumor growth factor, IFN interferon, GFAP glial fibrillary acidic protein, MBP myelin basic protein, TNF tumor necrosis factor, fMRI functional magnetic resonance imaging, *L. reuteri Lactobacillus reuteri*

**Table 1 Tab1:** Study schedule of enrollment, interventions, and assessments

	Study period				
	Screening	Baseline	Follow-up		Post-trial
Visit		1	2	3	
Time point		Day 0	Week 12	Week 24	Week 36
Enrollment					
Eligibility screening	X				
Written informed consent		X			
Randomization and allocation (after eligibility criteria met and written informed consent obtained)		X			
Interventions					
First stage: *L. reuteri* vs placebo			X		
Second stage: *L. reteri* plus OXT spray vs placebo plus OXT spray				X	
Assessments					
Past medical history and medications	X				
Surveys (ABC, SRS-2, GSI, and microbiome)		X	X	X	
Labs (OXT and fecal microbiome)		X	X	X	
Tests (emotion matching and eye-tracking)		X	X	X	
Adverse events			X	X	X

*OXT* oxytocin, *ABC* Aberrant Behavior Checklist, *SRS* social responsiveness scale, *GSI* gastrointestinal severity index, *GABA* gamma-aminobutyric acid, *IL* interleukin, *TGF* tumor growth factor, *IFN* interferon, *GFAP* glial fibrillary acidic protein, *MBP* myelin basic protein, *TNF* tumor necrosis factor, *fMRI* functional magnetic resonance imaging, *L. reuteri Lactobacillus reuteri*

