### Intervention

First stage: probiotic bacteria, *L. reuteri* (BioGaia), will be used in the study. It has been used in previous clinical trials, including those targeting pediatric populations [20–22]. Subjects will receive 10^10^ colony-forming units of *L. reuteri* daily or placebo for a duration of 3 months. *L. reuteri* has demonstrated consistently favorable safety profiles across multiple clinical trials [20–22].

Second stage: We chose to use syntocinon intranasal spray (Novartis pharmaceuticals) as it is currently the most commonly used standardized oxytocin nasal spray for clinical trials worldwide. Because patients with sensory difficulties need additional training, we will instruct the patient and family members to the use of spray, which begins with 1 puff of 4 IU daily, as well as provide training for MRI taking. After 1 week, the dose will increase to 1 puff per nostril for both nostrils daily (8 IU/day). After the second week, the dose will increase to 1 puff per nostril for both nostrils twice a day (16 IU/day). After the third week, the dose will titrate up to the maximum dose 24 IU daily, which is 2 puffs per nostril for both nostrils in the morning, and 1 puff per nostril for both nostrils in the afternoon. The dosage of 24 IU per day has been approved safe and adequate in even younger patients (ages 3–8 years old) by previous publications [23, 24].

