### Sample size and power calculation

This project is intended to evaluate the feasibility of implementing an oral supplementation of *L. reuteri* probiotics with and without an intranasal OXT spray therapy to inform an eventual larger-scale randomized trial that will allow for a more rigorous assessment of the efficacies of the proposed single or dual interventions. Hence, our sample size is calculated based solely on the primary outcomes: (1) scores of behavioral assessment questionnaires, including the ABC and SRS-2; (2) scores of objective ASD behavioral tests, including eye-tracking and emotional face matching tests; and (3) serum OXT changes. To achieve statistical power of 80% with an overall one-sided significance level of alpha = 0.10, if we assume a large effect size of 0.8 (Cohen’s *d*) in each of primary outcomes for the effect of *L. reuteri* probiotics alone vs *L. reuteri* probiotics plus OXT therapy, an estimated number of 26 ASD patients in each group would be needed based on independent two-sample *t* test. If a potential noncompliance or dropout rate of 10% is assumed, we plan to enroll 60 autistic subjects totally for this pilot study. Sample size calculation was carried out using the PASS 16 Power Analysis and Sample Size Software (NCSS, LLC. Kaysville, Utah).

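### The serious-adverse-event rule takes the patient out of the trial, not only off treatment, so as written it ends follow-up of the patients most informative about tolerability

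*Protocol article*

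**What the plan says.** The rule is one sentence in Safety and adverse effect reporting: "Randomized patients will have to be immediately withdrawn from the trial if they complain about serious adverse events". It is mandatory and immediate, and it makes no distinction by cause.

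The follow-up it would interrupt is set out in four places:

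- The same section states that "Adverse reactions will be monitored on a monthly basis via self-report and telephone check-in".
- Table 1 ("Study schedule of enrollment, interventions, and assessments") marks adverse events at weeks 12, 24 and 36, the last under a post-trial heading.
- Secondary outcomes and Data collection place all questionnaires and tests at weeks 0, 12 and 24.
- Data management and statistical analysis plan says "Analyses based on the intent-to-treat principle are designed to examine the treatment effect of" *L. reuteri* against placebo at the end of the first stage.

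Two provisions keep some information about a withdrawn patient. The event is reported: "All adverse events will be reported to the Human Research Committee promptly in accordance with guidelines". The feasibility data also include "reasons why patients chose not to participate, dropout rate, and reasons for dropout".

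**The concern.** Stopping study treatment and leaving the study are different things. The first protects the patient. The second protects nobody and discards data. The article states only the second, and no other section says that a patient withdrawn under this rule keeps attending visits or is followed until the event resolves.

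Two things are at stake:

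- **Safety.** Study design names intervention tolerability as something the pilot tests, and the Discussion says the focus is on acceptability and tolerability of the dual therapy. The patients with serious events would have their observation cut short. The fact of the event is kept. Its later course, and any later adverse events, may not be. Interim analysis and stopping guideline also allows the study to stop if adverse effects are too severe, and judging that calls for knowing how such events evolve.
- **The intent-to-treat comparison.** Outcomes would be missing because of harm that arose after randomization. This weakens the planned comparison without contradicting it.

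**Working it through.** The plan gives no figure on this point, so there is none to reproduce. Two checks follow.

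**1. Follow-up lost per affected patient**

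Inputs:

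- Treatment lasts 24 weeks (Study procedure).
- Post-baseline outcome visits are at weeks 12 and 24 (Data collection).
- Safety contacts are monthly (Safety and adverse effect reporting). I assume every 4 weeks, so weeks 4, 8, 12, 16, 20 and 24: six contacts.
- Oxytocin starts in week 13 (Abstract, Methods). Under Intervention it is given at 4, 8 and 16 IU/day in its first three weeks, and then "After the third week, the dose will titrate up to the maximum dose 24 IU daily". Week 16 is therefore the first week at full dose.

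| Event at | Monthly contacts lost | Outcome visits lost | Weeks lost to week 24 |
|---|---|---|---|
| Week 4 | 5 of 6 (weeks 8 to 24) | 2 of 2 | 24 − 4 = 20 |
| Week 16 | 2 of 6 (weeks 20, 24) | 1 of 2 | 24 − 16 = 8 |

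The week-36 check is left out of the count because its post-trial heading makes its status unclear.

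**2. Possible effect on the week-12 comparison (illustration only)**

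The article gives neither a serious-event rate nor a missing-data method for the primary outcomes. Suppose that:

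- k of 30 patients in one arm only are withdrawn in stage 1;
- each would have scored δ SD worse than those who stay;
- the analysis uses complete cases.

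The full-arm mean is then worse than the complete-case mean by (k/30) × δ, and SE = √(1/(30 − k) + 1/30) in SD units.

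| k | δ | Shift (SD) | SE (SD) | Shift/SE |
|---|---|---|---|---|
| 1 | 0.5 | 0.5/30 = 0.017 | √(1/29 + 1/30) = 0.260 | 6.4% |
| 2 | 1.0 | 2/30 = 0.067 | √(1/28 + 1/30) = 0.263 | 25.4% |
| 3 | 1.0 | 3/30 = 0.100 | √(1/27 + 1/30) = 0.265 | 37.7% |

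**Power.** Sample size and power calculation requires 26 per group and says "If a potential noncompliance or dropout rate of 10% is assumed, we plan to enroll 60 autistic subjects totally for this pilot study". The margin is 60 − 2 × 26 = 8 patients, or 4 per arm. Losses of 1 to 3 in one arm fit within it, so power is not the issue.

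**The case against.** The strongest reply is that the phrase is loose wording for stopping treatment. Nothing in the article says that later assessments are cancelled for these patients, and the full, IRB-approved protocol may say how they are followed. That is possible. But the rule is stated here rather than left out, and someone who follows the sentence as written would end the patient's participation.

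Several limiting points stand:

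- The week-36 check sits under a post-trial heading, so leaving the trial need not cancel it. The event and the reason for dropout are recorded in any case.
- The intent-to-treat analysis is specified for the end of stage 1. An event in stage 2 cannot affect it, because week 12 has already been measured. Only stage-1 events matter there, under a probiotic described as having a favourable safety record or under placebo.
- In stage 2 both arms receive oxytocin, so withdrawals related to it need not differ between arms.
- The rule names no cause, so the missing data need not be related to treatment.
- The number of affected patients is unknown and likely to be small among 60.

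These points narrow the effect on efficacy. They do not restore the safety follow-up that each affected patient would lose.

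**Conclusion.** The point holds as a defect in a stated rule. As worded, it ends the remaining outcome visits and monthly safety contacts of any patient with a serious adverse event: from 2 of 6 contacts and 1 of 2 outcome visits for an event at week 16, up to 5 of 6 contacts and both visits for one at week 4. These counts assume four-weekly contacts.

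The loss falls mainly on safety information, which matters because tolerability is an aim of the pilot. The efficacy effect is secondary and probably small. The illustrated range of 6% to 38% of a standard error rests wholly on assumed numbers of withdrawals, assumed differences in outcome and complete-case analysis. What remains uncertain is the authors' intent, the frequency of such events and the status of the week-36 check.

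**What to change.** Replace the sentence with wording such as:

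> Study treatment will be stopped after a serious adverse event. The participant remains in the scheduled week-12 and week-24 assessments and in adverse-event follow-up to week 36, unless consent for follow-up is withdrawn, and is analysed in the assigned arm.

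This keeps the authors' precaution of stopping treatment and uses visits and contacts already scheduled. The cost is a one-sentence amendment plus follow-up of participants who are off treatment. That burden is real: visits include blood and stool samples, eye-tracking and emotion matching, and participants may be as young as 3. Where a full visit is too much after a serious event, the adverse-event contacts and the ABC and SRS-2, which a caregiver or other informant completes, could be kept as a minimum.

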### Interim analysis and stopping guideline

We plan to conduct an interim analysis at 12 weeks. We will stop the study if adverse effects or toxicities are too severe, data quality is poor, accrual is slow, and adherence to treatment is unacceptably low, or if study integrity has been undermined by fraud or misconduct.

### Feasibility target

Feasibility targets will be set to greater than or equal to 30 enrollments per 6 months, greater than or equal to 70% adherence rate, and greater than or equal to 70% data collection completion rate.

## Discussion

This study is the first pilot and feasibility study that explores the implementation of a psychotropic *L. reuteri* probiotics strain alone and in combination with exogenous OXT administration as a treatment for ASD symptoms. The description of this protocol followed SPIRIT guidelines. Although multiple OXT-related ASD clinical trials have been conducted, this is also the first clinical study designed to investigate the synergistic relationship between *L. reuteri* probiotics and exogenous OXT administration in an autism treatment. As this is a pilot and feasibility study, we have specified and examined the primary and secondary outcomes that we would use in a larger, randomized clinical trial in the future. We plan to focus on the acceptability and tolerability of *L. reuteri* probiotics and OXT dual therapy in ASD patients and refine the study protocol. The secondary aims could help us to explore future mechanistic research.

We include both subjective and objective social-behavioral tests to quantify different aspects of ASD behavior as primary outcomes. Of note, a new video-based eye-tracking device developed by Kong et al. [29] could assess fixation/attention to human body parts such as the mouth and regions around the eye. The test can achieve sensitivity of 93% and specificity of 86% in distinguishing ASD and non-ASD individuals [26]. In addition, an emotional facial matching paradigm has to be used to objectively assess ASD patients’ ability to detect and characterize human emotions in another ASD drug trial [27].

Based on our currently mechanistic understanding of the roles of *L. reuteri* and OXT in OXT signaling/gut-brain axis [14, 15], in our secondary aim, we proposed to explore whether GI functions and gut microbiome and short-chain fatty acid metabolite profiling may be altered by either *L. reuteri* therapy alone or *L. reuteri* plus OXT therapy. Apart from OXT levels, microbial relative abundances and diversity and fecal short-chain fatty acid metabolites are proposed for compliance assessment.

The study intervention builds upon prior research on the role of *L. reuteri* probiotics on the gut-brain axis through the immune system; a recent systematic review suggests cytokine aberrations in ASD patients, such as IL-1beta, IL-6, TGF-beta, and interferon-gamma [31]. They might correlate with markers that directly signify neuronal/glial injury such as S100B [32, 33], myelin basic protein (MBP) [34], and glial fibrillary acidic protein (GFAP) [35]. Several other neurotransmitters have been implicated in the pathophysiology of ASD, including GABA, serotonin, and dopamine [20, 21, 36]. All of them are also known to interact with OXT signaling pathway. Levels of platelet-free plasma GABA are significantly elevated in ASD patients. Specifically, high blood plasma levels of GABA are associated with reduced GABA levels in the ASD brain, which leads to the hypothesis that imbalance in GABA would contribute to social deficits commonly seen in ASD patients. Further, animal studies showed that the introduction of oxytocin to the ASD mice is capable of alleviating social deficits by restoring an interrupted developmental switch from GABA as an excitatory neurotransmitter to an inhibitory neurotransmitter [36]. Derangement in the serotonin system is proposed to play a role in ASD due to its pleiotropic effects across multiple neuronal systems throughout development, and elevated whole blood serotonin is present in more than 25% of ASD children [22]. OXT may inhibit serotonin signaling [20], consistent with the finding that OXT and whole blood 5-HT levels in ASD subjects consistently display a negative correlation [24]. Conversely, OXT and dopamine may have synergistic functions, as OXT facilitates dopamine release in particularly the midbrain striatal nucleus accumbens, mediating reward processing related to social functions [21]. Similar to OXT, plasma dopamine is decreased in ASD children [37], although it is not clear whether baseline dopamine level/signaling is decreased at the neuronal level in patients with ASD. As a strength of this pilot study, the applicability and feasibility of blood and fecal sample collection is being piloted in this trial of ASD patients. Results from this study will inform a well-designed mechanistic research to identify and validate any potential biomarker as a reliable predictor of OXT-based therapy in the future.

We hope that this pilot study will serve as a starting point to address any potential roles of *L. reuteri* probiotic induced endogenous OXT in ASD. If significant correlations are found, we would like to confirm the results of the pilot study on a larger scale. The results from this pilot study will provide important proof-of-concept information that will serve as the basis for further scientific studies. We hope that information generated by our research will help to assess and promote the development of effective therapeutic interventions to treat the behavioral symptoms in ASD patients.

## Data Availability

All manuscripts must include an “Availability of data and materials” statement. Data availability statements should include information on where data supporting the results reported in the article can be found including, where applicable, hyperlinks to publicly archived datasets analyzed or generated during the study. By data, we mean the minimal dataset that would be necessary to interpret, replicate and build upon the findings reported in the article. We recognize it is not always possible to share research data publicly, for instance when individual privacy could be compromised, and in such instances, data availability should still be stated in the manuscript along with any conditions for access.

## Abbreviations

ABC: Aberrant behavior checklist
ADI-R: Autism Diagnostic Interview-Revised
ADOS: Autism Diagnostic Observation Schedule
ASD: Autism spectrum disorders
BOLD: Blood oxygen level dependent
BVP: Blood volume pulse
CGI-I: Clinical global impression-improvement
CONSORT: Consolidated Standards of Reporting Trials
DSM: Diagnostic and Statistical Manual of Mental Disorders
EDA: Electrodermal activity
GABA: Oxytocin-mediated neuroprotective γ-aminobutyric acid
GFAP: Glial fibrillary acidic protein
GI: Gastrointestinal
HRV: Heart rate variability
IL-1: Interleukin 1
IL-6: Interleukin 6
MBP: Myelin basic protein
OXT: Oxytocin
RCT: Randomized controlled trials
SAR: Specific absorption rate
SRS: Social responsiveness scale
